**Fig. 1 f0005:**
[figure not shown]
Timeline of the 12-month pragmatic, single-arm HAPpEN trial from the patient's perspective. At the start, next to nutrition and behavioral education, a comprehensive medical history is taken including detailed anamnesis via surveys and a standardized physical examination (body height, weight respectively body mass index (BMI), waist circumference, blood pressure, heart and pulse rate, joint function, thoracic auscultation, abdominal examination, motor and sensory tests), supplemented by ergometry and lab tests to assess patients' fitness level and health status. Monthly appointments with general practitioners and group sessions with physiotherapists support patients in identifying performance goals and increasing muscle-strengthening exercises or physical activity in general. The HAPpEN app acts a stepwise digital diary, allowing for education and monthly nutrition and exercise goals to be set, aided by video-based training. Follow-up physical examinations are conducted at six and 12 months. Additionally, patients' perceptions of social group interactions, dynamics and social media usage are continuously assessed and documented through surveys and interviews.

**Table 2 t0010:** Data Collection within the 12-month pragmatic HAPpEN trial.^2^

	Enrolment	Pragmatic trial (months)										Trial End	Instrument	Statistics
Timepoint	1	2	3	4	5	6	7	8	9	10	11	12		
Social anamnesis	x												questionaire	Person‘s-chi-squared test
Body weight management	x												questionaire	
Wellbeing/quality of life/sleep	x/x/x^3^					−/(x)/x						x/x/x	questionaire	Analysis of Variances, t-test
Medical history (smoking, joint trouble)	x					x						x	questionaire	Cochran's Q test, Friedmann test
BMI^1^, weight, waist circumference, blood pressure, blood test, thorax-, abdomen-, neurological tests, ergometry	x					x						x	medical examination	Analysis of Variances
Medication	x					x						x	questionaire, medication plan	Cochran's Q test
Family history and diseases	x												questionaire	
Nutrition literacy eating/drinking behavior	x					x						x	questionaire	Cochran's Q test
Physical literacy and activity	x					x						x	questionaire	Cochran's Q test
HAPpEN-App												x	questionaire	t-test, correlation, regression
Technical affinity	x												questionaire	
Social support/social network	x					x						x	questionaire/ interviews/	
General practitioner-centered program						x						x	questionaire/ interviews	

^1^BMI, body mass index

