^2^Data will be collected at indicated time points using shown measurement instruments. Statistical evaluation is performed utilizing the specified test.

^3^The consecutive Xs represent the individual assessments of wellbeing, quality of life, and sleep at the indicated time points. If three Xs are present, all three assessments were conducted at that time point; if only two Xs are present, only two assessments were performed accordingly.

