#### Recommendations for diet and physical activity

2.4.3

Instead of focusing on calorie counting, participants receive nutrition guidance, mainly based on the mediterranean diet. Emphasis is placed on consuming foods with low energy density (Stelmach-Mardas et al., 2016). For physical activity, recommendations focus on daily walking, moderate-to-vigorous physical activity, and strength exercises (World Health Organization, 2020). Finally, sleep is discussed as an important additional health behavior.

Step-wise goals across 17 topics (see Supplementary Table 5) related to weight management and health promotion (Schlesinger et al., 2019; *Forschungs und Prax der Gesundheitsförderung. Published online*, 2017) are designed to be challenging, achievable and tailored to individual performance and circumstances (Quintiliani et al., 2014). Topics cover areas such as reducing soft drinks, snacks and fast food, increasing plant-based protein, physical activity, and daily steps, improving sleep behavior and reducing sedentary time. Participants are advised to tackle two to three topics each month. Within each topic, participants are asked to select a challenging goal out of a list of five to eight options ranging from “I am not aware of how to address this topic in my daily life” (with the aim to track their behavior to identify areas for change) to “reduce bad habits and improve lifestyle up to six to seven days/week”. General practitioners assist with background information and goal setting as needed.

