### Measures

2.5

Primary outcomes include BMI, body weight, waist circumference, blood parameters (e.g. Hemoglobin A1c, lipid metabolism and uric acid), blood pressure and heart rate. Secondary outcomes comprise:•Quality of life (Morfeld and Bullinger, 2008), wellbeing, anxiety (Spitzer et al., 1999) and disease burden (e.g. medication, comorbidities, sleeping behavior)•Nutrition, health and physical activity literacy as well as health behavior change for an improved understanding of patients' personal health status (Spitzer et al., 1999; Westenhöfer et al., 2003; Bull et al., 2009; Pfeiffer et al., 2020)•Benefit and effectiveness of social interaction (Borek et al., 2019; Carrillo-Álvarez et al., 2019; Nackers et al., 2015)•Acceptance, efficiency, user-friendliness and -experience of digital therapy support by evaluating self-reported application usage frequency and its most relevant features (Cheah et al., 2022; Laugwitz et al., 2008; Sekhon et al., 2022)•Economic evaluation through literature-based modeling of the costs and their assessment relative to the generated benefits

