### Statistics

2.6

BMI and body weight will be compared between the patients in the trial and those receiving current obesity standard care. Furthermore, outcomes will be analyzed at baseline and after six and 12 months, using paired *t*-tests, analysis of variances, Cochran's Q or Friedman test (see Table 2). Data distribution will be analyzed using Shapiro-Wilk normality test and histograms.

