### Baseline demographic characteristics of the trial population

3.1

The baseline population consisted of 98 German participants with a mean age of 46.9 ± 11.8 years, slightly higher than the national average and average from the federal stat of Bavaria (Statistische Bibliothek, 2022). Most participants were female (74.1 %) and married, cohabitating with their spouse (64.3 %) (see Table 3). Compared to national averages, higher proportions had secondary education (43.5 %) and professional training (62.2 %), but fewer held high school diplomas (20.0 %) or university entrance qualifications. The majority (83.3 %) were employed, with 14.5 % working in shift-based jobs.

**Table 3 t0015:** Demographic characteristics and weight history of the baseline population (98 German adults), assessed at the start of the HAPpEN trial in May/June 2023.

Demographic characteristics	baseline population	Weight history	baseline population
**Gender** Female/Male	74.1 % (63) / 25.9 % (22)	**Childhood Overweight**	59.8 %
**Age**	46.9 ± 11.8 years (83)	**Previous Weight Loss Attempts**	96.6 % (84)
**Practice Affiliation** Oberlandärzte Marktleugast [name]/[name] Presseck [name]/[name] Untersteinach [name]/[name] Thurnau [name] Kasendorf [name] Stadtsteinach	52.0 % (51) 5.1 % (5) 6.1 % (6) 16.3 % (16) 13.3 % (13) 7.1 % (7)	**Years Spent on Weight Reduction** 10 years five to nine years two to four years < two years	67.1 % (55) 18.3 % (15) 7.3 % (6) 7.3 % (6)
**Marital Status** Single, living alone Single, living with a partner Married, living with spouse Married, living separately Divorced Widowed	13.1 % (11) 14.3 % (12) 64.3 % (54) 1.2 % (1) 6.0 % (5) 1.2 % (1)	**Causes/Triggers of Weight Gain** Life changes: career change, relocation, retirement Changes in family environment: pregnancy, children, marriage, divorce Decreased physical activity Unbalanced diet Menopause/hormonal changes Medications/underlying health conditions Increased alcohol consumption Smoking cessation Other: stress, fieldwork, acute illness/injury, bullying, exam situations	13.6 % (12) 51.1 % (45) 63.6 % (56) 58.0 % (51) 28.4 % (25) 34.1 % (30) 5.7 % (5) 17.0 % (15) 13.6 % (12)

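### Table 2 fixes Cochran's Q, a test for yes/no data only, as the sole analysis of the literacy, eating-behaviour and activity outcomes, without stating that these are yes/no items

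*Protocol article*

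**What the plan says.** Table 2 of the protocol article (section 2.4.2) lists each group of measures with its time points, instrument and test. For "Nutrition literacy eating/drinking behavior" and for "Physical literacy and activity" the instrument is a questionnaire, the time points are enrolment, month 6 and month 12, and the only test named is Cochran's Q.

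The footnote to the table makes this an instruction: "Statistical evaluation is performed utilizing the specified test". Section 2.6 (Statistics) lists paired t-tests, analysis of variance, Cochran's Q and Friedman for the comparisons over time, and refers to Table 2 for which goes where.

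Section 2.5 (Measures) places the outcomes among the secondary ones: "Nutrition, health and physical activity literacy as well as health behavior change for an improved understanding of patients' personal health status". It cites sources for the instruments but gives no scale, scoring rule or cut-off.

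**The concern.** Cochran's Q compares the proportion of successes across repeated measurements on the same people. Its input is a 0/1 value per person and visit; it is not defined for a score, an ordered category or a quantity. These two rows cover literacy, eating and drinking behaviour and physical activity, where scores, frequencies and amounts would be natural. For any such measure the named test is either inapplicable or needs a yes/no cut.

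The cut would have two costs. It discards information, so a real change over the year is more likely to be missed. It also makes the result depend on where the line is drawn, and the article draws none.

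This matters because the abstract's conclusion and section 5 present better health literacy as an aim of the programme, and these rows hold its evidence. It is a point about a stated choice of test rather than about omitted detail: the article assigns the test and says that it is the one to be used.

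**Working it through.** **Table 2, row by row**

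| Row | Instrument | Test assigned |
|---|---|---|
| Wellbeing, quality of life, sleep | questionnaire | ANOVA, t-test |
| Medical history (smoking, joints) | questionnaire | Cochran's Q, Friedman |
| BMI, weight, waist, blood pressure, blood tests and other examinations | medical examination | ANOVA |
| Medication | questionnaire, medication plan | Cochran's Q |
| Nutrition literacy, eating/drinking | questionnaire | Cochran's Q |
| Physical literacy and activity | questionnaire | Cochran's Q |

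Other questionnaire rows have a test for scores or ranks. The two rows at issue share the assignment given to medication, where taken/not taken is a natural coding.

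**Cost if a score is dichotomised**

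The article gives 98 participants at baseline. It states no power, effect size, standard deviation or correlation for these outcomes, so there is no figure to reproduce. Everything below rests on assumptions that are not in the document: a normally distributed score, equal correlation ρ between the three visits, two-sided α = 0.05, and an effect large enough to give repeated-measures ANOVA 80% power.

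*Relative efficiency.* With a cut at c that leaves a proportion p above it,

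ARE = φ(c)² / [p(1 − p)] × (1 − ρ) / (1 − ρ_bin),

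where ρ_bin is the between-visit correlation of the 0/1 variable. For a median split, c = 0 and p = 0.5. The first factor is then 0.3989² / 0.25 = 0.637, and ρ_bin = (2/π)·arcsin(ρ).

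At ρ = 0.5: ρ_bin = 0.333 and ARE = 0.637 × 0.5 / 0.667 = 0.477. Splitting the score is thus like keeping about 48% of the participants.

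*Power.* The omnibus test over three visits has 2 degrees of freedom and critical value 5.99. Power of 80% needs a noncentrality of 9.63. Multiplying by the ARE and reading power from the noncentral chi-square gives:

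| ρ | ARE | Noncentrality | Power of Q | Relative loss from 80% |
|---|---|---|---|---|
| 0 | 0.637 | 6.13 | 59% | 26% |
| 0.3 | 0.553 | 5.33 | 53% | 34% |
| 0.5 | 0.477 | 4.60 | 47% | 41% |
| 0.7 | 0.377 | 3.63 | 38% | 52% |
| 0.8 | 0.311 | 2.99 | 32% | 60% |

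*Other assumptions.*
- Cut at the 80th percentile: 48% at ρ = 0 and 35% at ρ = 0.5, so an off-centre cut loses more.
- Reference power 95% at ρ = 0.5: 68%, a relative loss of 28%, so a large effect is hurt less.

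*Simulation check* (4,000 runs, 98 participants, linear change over the visits, median split):

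| ρ | ANOVA | Friedman | Cochran's Q | Q relative to Friedman |
|---|---|---|---|---|
| 0.3 | 80% | 65% | 54% | −17% |
| 0.5 | 80% | 64% | 45% | −29% |
| 0.7 | 79% | 63% | 39% | −39% |

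A separate simulation with 80 complete participants, ρ = 0.5 and a sustained shift of 0.30 SD gave 80%, 65% and 44%. There Q loses 32% relative to Friedman, so the result does not hinge on the shape of the change.

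**The case against.** The strongest reply is that the article never says these questionnaires yield scores. Table 2 calls the instrument only a questionnaire, and section 2.5 gives domains and citations. If the items are yes/no or correct/incorrect and are analysed one at a time, Cochran's Q is valid and nothing is cut. The table also varies its tests by row, as authors would who had matched test to data type and expected categorical items here. Scoring rules and cut-offs commonly sit in the full protocol or analysis plan, so nothing shows that a cut-point would be chosen after seeing the data.

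This stands in part. It rules out saying that the plan forces graded measures to be dichotomised, which a reader might infer. It does not rescue the two cells as written. If an unseen document sets cut-offs, the cost above applies; if it gives another test for scores, it disagrees with Table 2 and its footnote. The rows are safe only if every item in them is truly binary, which the article does not say.

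Two further inferences are tempting and unsupported:

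- Section 2.4.3 asks participants to "select a challenging goal out of a list of five to eight options". This might be read as proof that the outcomes are graded. It describes goals within the intervention, not the questionnaires at enrolment, month 6 and month 12.
- A reader might conclude that almost half the power is lost. That matches one scenario, near ρ = 0.5 with a median split and ANOVA as comparator. Other reasonable assumptions give a quarter or 60%, and the loss against Friedman is smaller.

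It is also fair that lack of an effect size is not peculiar to Cochran's Q. Friedman and ANOVA omnibus tests share it, and proportions per visit can be reported beside Q.

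**Conclusion.** The point holds in conditional form. The article fixes a binary-only test as the sole analysis of two groups of secondary outcomes without saying that they are binary. For any of them held as a score, ordered category or amount, the test cannot be used without a cut that the article does not define.

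Under the assumptions listed, such a cut would cost 26% to 60% of the power of repeated-measures ANOVA across correlations from 0 to 0.8. It would cost a little under a third of the power of Friedman at ρ = 0.5. None of the inputs to those figures comes from the article, so they indicate a range and do not estimate this trial's loss. For true yes/no items the loss is nil.

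The consequence is limited to these secondary outcomes. It deserves correction because health literacy is a stated focus and the change is cheap.

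**What to change.** In the two rows of Table 2, state which items are yes/no and which are scores, ordered categories or amounts, and assign tests accordingly:

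- **Scores and amounts:** a linear mixed model or repeated-measures ANOVA over the three visits, with Friedman if the measure is ordinal or clearly skewed. Report the baseline-to-12-month change with a 95% CI.
- **True yes/no items:** keep Cochran's Q and report the proportion at each visit.

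ANOVA and Friedman are already listed in section 2.6. The mixed model has the added advantage of using participants who miss a visit, whereas Cochran's Q, Friedman and classical repeated-measures ANOVA need all three values.

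The cost is two table cells and the matching analysis code. No new data are needed. The change should be made, and dated, before the follow-up answers in these rows are analysed.

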#### Recommendations for diet and physical activity

2.4.3

Instead of focusing on calorie counting, participants receive nutrition guidance, mainly based on the mediterranean diet. Emphasis is placed on consuming foods with low energy density (Stelmach-Mardas et al., 2016). For physical activity, recommendations focus on daily walking, moderate-to-vigorous physical activity, and strength exercises (World Health Organization, 2020). Finally, sleep is discussed as an important additional health behavior.

Step-wise goals across 17 topics (see Supplementary Table 5) related to weight management and health promotion (Schlesinger et al., 2019; *Forschungs und Prax der Gesundheitsförderung. Published online*, 2017) are designed to be challenging, achievable and tailored to individual performance and circumstances (Quintiliani et al., 2014). Topics cover areas such as reducing soft drinks, snacks and fast food, increasing plant-based protein, physical activity, and daily steps, improving sleep behavior and reducing sedentary time. Participants are advised to tackle two to three topics each month. Within each topic, participants are asked to select a challenging goal out of a list of five to eight options ranging from “I am not aware of how to address this topic in my daily life” (with the aim to track their behavior to identify areas for change) to “reduce bad habits and improve lifestyle up to six to seven days/week”. General practitioners assist with background information and goal setting as needed.

#### Educational sessions led by nutrition and behavior change experts

2.4.4

In three 90-min sessions at accessible located venues, nutrition and behavior change experts provide evidence-based guidance on diet, physical activity and behavior change strategies. These sessions focus on the rationale, practical application and techniques like step-wise adherence, action and coping planning, grounded in cognitive behavioral theory.

#### Activities led and supported by physiotherapists

2.4.5

HAPpEN involves monthly physiotherapists-led group sessions tailored to participants' fitness levels and local accessibility. These sessions teach safe, effective exercise for home or group practice, minimizing injury risk and supporting consistency. Animated tutorials in the app supplemented home practice, allowing physiotherapists for personalized adjustments based on participants' feedback.

#### Digital website and app for self-monitoring and social support

2.4.6

The HAPpEN app and website provides tools for self-monitoring, including tracking dietary and activity goals, weight progress and personalized training plans with animated tutorials (see Fig. 2). Participants can access recipes, educational modules and challenges to support a healthy lifestyle with direct communication through the app-linked chat function for consultation with physicians and physiotherapists. A closed forum facilitates peer exchange on tips, challenges, successes, and event announcements. Initial training and ongoing support promote effective app usage.

**Fig. 2 f0010:**
[figure not shown]
Screenshots of the HAPpEN app (A) and homepage (B) as integrated digital support tools in HAPpEN. (A) The HAPpEN-app functioned as a personalized patient diary, facilitating feedback, self-management and -monitoring. It included a planner for goal setting and weight tracking, with automatically generate overviews (e.g. weight trajectory curves) based on user input to provide feedback on weight management. (B) The HAPpEN homepage page offered educational content on health-promoting lifestyles, accessible via news page but also via app. Additionally, it featured weekly edutainment challenges, announcements for social events, and a forum for participant exchange.

#### Additional in-person opportunities for social support

2.4.7

Social support was further provided via monthly sessions, as well as regionally accessible cooking and hiking events, promoting engagement and community-building.

### Measures

2.5

Primary outcomes include BMI, body weight, waist circumference, blood parameters (e.g. Hemoglobin A1c, lipid metabolism and uric acid), blood pressure and heart rate. Secondary outcomes comprise:•Quality of life (Morfeld and Bullinger, 2008), wellbeing, anxiety (Spitzer et al., 1999) and disease burden (e.g. medication, comorbidities, sleeping behavior)•Nutrition, health and physical activity literacy as well as health behavior change for an improved understanding of patients' personal health status (Spitzer et al., 1999; Westenhöfer et al., 2003; Bull et al., 2009; Pfeiffer et al., 2020)•Benefit and effectiveness of social interaction (Borek et al., 2019; Carrillo-Álvarez et al., 2019; Nackers et al., 2015)•Acceptance, efficiency, user-friendliness and -experience of digital therapy support by evaluating self-reported application usage frequency and its most relevant features (Cheah et al., 2022; Laugwitz et al., 2008; Sekhon et al., 2022)•Economic evaluation through literature-based modeling of the costs and their assessment relative to the generated benefits

### Statistics

2.6

BMI and body weight will be compared between the patients in the trial and those receiving current obesity standard care. Furthermore, outcomes will be analyzed at baseline and after six and 12 months, using paired *t*-tests, analysis of variances, Cochran's Q or Friedman test (see Table 2). Data distribution will be analyzed using Shapiro-Wilk normality test and histograms.

## Results

3

### Baseline demographic characteristics of the trial population

3.1

The baseline population consisted of 98 German participants with a mean age of 46.9 ± 11.8 years, slightly higher than the national average and average from the federal stat of Bavaria (Statistische Bibliothek, 2022). Most participants were female (74.1 %) and married, cohabitating with their spouse (64.3 %) (see Table 3). Compared to national averages, higher proportions had secondary education (43.5 %) and professional training (62.2 %), but fewer held high school diplomas (20.0 %) or university entrance qualifications. The majority (83.3 %) were employed, with 14.5 % working in shift-based jobs.

**Table 3 t0015:** Demographic characteristics and weight history of the baseline population (98 German adults), assessed at the start of the HAPpEN trial in May/June 2023.

Demographic characteristics	baseline population	Weight history	baseline population
**Gender** Female/Male	74.1 % (63) / 25.9 % (22)	**Childhood Overweight**	59.8 %
**Age**	46.9 ± 11.8 years (83)	**Previous Weight Loss Attempts**	96.6 % (84)
**Practice Affiliation** Oberlandärzte Marktleugast [name]/[name] Presseck [name]/[name] Untersteinach [name]/[name] Thurnau [name] Kasendorf [name] Stadtsteinach	52.0 % (51) 5.1 % (5) 6.1 % (6) 16.3 % (16) 13.3 % (13) 7.1 % (7)	**Years Spent on Weight Reduction** 10 years five to nine years two to four years < two years	67.1 % (55) 18.3 % (15) 7.3 % (6) 7.3 % (6)
**Marital Status** Single, living alone Single, living with a partner Married, living with spouse Married, living separately Divorced Widowed	13.1 % (11) 14.3 % (12) 64.3 % (54) 1.2 % (1) 6.0 % (5) 1.2 % (1)	**Causes/Triggers of Weight Gain** Life changes: career change, relocation, retirement Changes in family environment: pregnancy, children, marriage, divorce Decreased physical activity Unbalanced diet Menopause/hormonal changes Medications/underlying health conditions Increased alcohol consumption Smoking cessation Other: stress, fieldwork, acute illness/injury, bullying, exam situations	13.6 % (12) 51.1 % (45) 63.6 % (56) 58.0 % (51) 28.4 % (25) 34.1 % (30) 5.7 % (5) 17.0 % (15) 13.6 % (12)
**Education** No formal qualification Basic education Secondary education High school diploma	1.2 % (1) 35.3 % (30) 43.5 % (37) 20.0 % (17)	**Reason for planned weight loss** Improved well-being and body image Life changes Improved health status Pain reduction Improved physical fitness/muscle building Other: engaging in hobbies, role model for children	96.6 % (85) 28.4 % (25) 89.8 % (79) 51.1 % (45) 78.4 % (69) 3.4 % (3)
**Vocational Training** No qualification Apprenticeship/vocational training Technician/Master's/Further education University of Applied Sciences/ University degree	6.1 % (5) 62.2 % (51) 23.2 % (19) 8.5 % (7)	**Barriers to Weight Management** Strong physical hunger Eating behavior Psychological issues: depression, attention-deficit-hyperactivity disorder, attention-deficit disorder, psychosis, eating disorders Health issues: underlying conditions, pain-related limitations Lack of physical activity Insufficient time or stress in daily life Societal, private, and professional obligations Other: lack of motivation, medication use, shift work	19.3 % (17) 56.8 % (50) 21.6 % (19) 26.1 % (23) 81.8 % (72) 56.8 % (50) 56.8 % (50) 11.4 % (10)
**Employment Status** Retired Unemployed Employed Student	9.5 % (8) 6.0 % (5) 83.3 % (70) 1.2 % (1)	**Previously Used Weight Loss Methods** Dietary changes/diets: e.g., calorie counting (with app), Zanadio app, Weight Watchers, intermittent fasting, shakes, “Losing Weight with Pleasure,” Oviva app, Bonvita, “Slim in Your Sleep” Physical activity: rehabilitation sports, fitness centers Behavioral therapy: e.g., self-monitoring, acquiring nutritional competence, Weight Watchers, Zanadio app, Oviva app Social reinforcement: e.g., Weight Watchers – group therapy, Zanadio app – counseling, Oviva app – counseling, psychotherapy, patient groups, family support Medications	89.4 % (76) 30.6 % (26) 34.1 % (29) 37.6 % (32) 2.4 % (2)
**Working Hours**	32.5 ± 10.4 h/week (75)	**Weight Loss Achieved by previous methods**	91.5 % (75)
**Shift Work**	14.5 % (11)	**Occurrence of Yo-Yo Effect following previous methods**	91.8 % (78)
**Smoking Status** Current smoking status (years / cigarettes/day) Former smoker Duration of smoking cessation (years)	20.0 ± 12.1 (8) / 18.0 ± 10.6 (9) 35.6 % (31) 13.9 ± 9.9 (31)	**Weight Monitoring** Daily Three times/week One to two times/week once/week never	12.8 % (11) 15.1 % (13) 26.7 % (23) 33.7 % (29) 11.6 % (10)

